**Fig. 2 Fig2:**
[figure not shown]
Design overview

**Table 1 Tab1:** Assessments by time point

	Screen	Baseline 1	Baseline 2	Each session	12 weeks/end-of-treatment	6, 9, 12 months	18, 24, 30, and 36 months
*Screening fully*							
Medical diagnosis, current smoking, and other inclusion/exclusion criteria	X						
Cognitive functioning (MMSE [43])	X						
*Participant characteristics*							
Demographics (age, race, etc.)		X					
Medical and smoking history		X					
Nicotine dependence (FTND [50])		X					
Motivation to quit (contemplation ladder [51])		X	X				
MN withdrawal scale [52]			X				
*Primary outcomes*							
Current smoking/smoking since last contact		X	X	X	X	X	X
Use of other tobacco products		X	X	X	X	X	X
Saliva sample for cotinine testing			X		X	X	
Exhaled breath sample for CO testing			X		X	X	
Depressive symptoms (PHQ-9 [53])		X	X		X	X	X
Depressive symptoms (CESD-10 [66])		X	X		X	X	
*Secondary outcomes*							
Positive and negative affect (PANAS [57])		X	X		X	X	X
Reactive anhedonia (SHAPS [68, 69])		X	X		X	X	
Perceived stress scale (PSS-4 [70])		X			X	X	
Health related quality of life (SF-12 [71])		X			X	X	
Exercise tolerance (DASI [72])		X			X	X	
MACE/mortality					X	X	X
Adverse event monitoring			X	X	X	X	X
*Hypothesized BA mediators*							
Pleasant/valued activities (BADS [76], PES [79, 80])		X			X	X	
*Acceptability*							
Treatment acceptability (CSQ-8 [81])					X		
*Potential confounders*							
Medication adherence questions [88, 89]		X			X	X	
Diet/exercise questions [92]		X			X	X	
Counseling sessions attended				X			
Cardiac rehabilitation attendance					X	X	
Outside of study depression treatment					X	X	
Outside of study smoking cessation treatment					X	X	

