[58], which provides an overview of why a heart attack happens, what happens after a heart attack (i.e. medications, lifestyle changes, cardiac rehabilitation), emotional responses to having a heart attack, and provides strategies for preventing future cardiac events, including medication adherence, weight management, smoking cessation, limiting alcohol intake, and engaging in physical activity. For sessions 3–6 in the control condition, participants will choose one of the following health topics to discuss: (1) Heart Healthy Nutrition, (2) Fruits and Vegetables, (3) Sleeping Well, (4) Screenings and check-ups, (5) Staying Hydrated, and (6) Communication with your providers. Previous work by our team using similar health education content showed it has no significant effect on mood during smoking cessation [60]. Each education component will be explicitly linked to cardiac health as the content is introduced. To maintain the integrity of our independent variable, we chose topics that are relevant to cardiac health, but do not directly address mood or smoking cessation.

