#### Potential confounders

We will collect data at all follow-ups on potential confounders of treatment effects so we can control for these variables as needed in analyses (i.e., data on dose of treatment received, cardiac rehabilitation attendance, depression or smoking counseling or medication use outside of the study, engagement in exercise, diet, and adherence to medications).

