#### Primary outcome analyses

We will estimate the effect of the interventions on smoking cessation (biochemically verified 7-day point prevalence abstinence) at end-of-treatment and follow-ups (6, 9 and 12 months) using a longitudinal regression model implemented with generalized estimating equations (GEE) with robust standard errors [91, 92]. Specifically, we will regress smoking status on intervention group (BAT-CS vs. control) and potential covariates (cardiac rehabilitation attendance, cessation treatment outside of the study, other baseline variables will be included as covariates if they are both not balanced by randomization and are correlated with the outcome under consideration at *p* < 0.10 level) using binomial errors, a logit link function, and a working unstructured correlation to accommodate within-subject correlation.

We will use a series of longitudinal mixed effects regression models to estimate the effect of BAT-CS versus control on depressed mood (PHQ-9) at end-of-treatment and subsequent follow-ups, controlling for baseline depression, cardiac rehabilitation attendance, depression treatment outside of the study, and any other variables not balanced by randomization that are correlated with depressed mood at follow-ups at a modest *p* < 0.10 level. Models will include a subject-specific intercept to adjust for repeated measurements within participant over time. Modeling is done using a likelihood-based approach and thus makes use of all available data (on the intent to treat sample) without directly imputing missing outcomes, to produce consistent estimates of the regression parameters.

For primary outcomes (i.e., biochemically verified 7-day point prevalence abstinence and PHQ-9) we will conduct a per-protocol analysis (with parallel models to those described above) to assess differences between groups among those who completed a substantial number of treatment sessions. Per protocol will be defined completing at least four treatment sessions in both treatment groups.

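### The PHQ-9 model includes, and the abstinence model appears to include, covariates measured only after randomisation that treatment arm can plausibly change

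*Protocol article*

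**What the plan says.** All references are to the protocol article.

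- **PHQ-9 model (Primary outcome analyses).** The longitudinal mixed model is specified as "controlling for baseline depression, cardiac rehabilitation attendance, depression treatment outside of the study", plus any other imbalanced variable correlated with mood at follow-up. No condition is attached to the named covariates.
- **Abstinence model (same section).** Smoking status is regressed on arm, with this list: "potential covariates (cardiac rehabilitation attendance, cessation treatment outside of the study, other baseline variables will be included as covariates if". The conditions that follow are imbalance after randomisation and correlation with the outcome at p < 0.10.
- **Rationale (Potential confounders).** The reason given for collecting these variables is: "We will collect data at all follow-ups on potential confounders of treatment effects so we can control for these variables as needed in analyses".
- **Timing (Table 1).** The rows "Cardiac rehabilitation attendance", "Outside of study depression treatment" and "Outside of study smoking cessation treatment" are marked at 12 weeks and at 6, 9 and 12 months. None is marked at Screen, Baseline 1 or Baseline 2.
- **Randomisation.** It takes place 1 week after discharge, directly after Baseline 2.
- **Secondary outcomes (Secondary outcome analyses).** The other abstinence outcomes use a similar strategy to the primary GEE. The other mood, quality-of-life and functional scales use models parallel to the PHQ-9 model.

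No section names a primary analysis without these covariates.

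**The concern.** A confounder of a treatment comparison has to influence, or share a cause with, who receives which treatment. Randomisation rules that out for anything arising afterwards. The stated reason for adjusting therefore does not apply to variables first recorded at 12 weeks.

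Adjusting for such a variable is not harmless if arm can shift it. The model then compares arms among people with the same attendance or the same outside treatment, and those subgroups were not formed by randomisation. Aim I asks about the efficacy of BAT-CS versus control, which is the total effect of being assigned to it. At stake is whether the arm coefficient in the confirmatory models still estimates that effect. The wording about other baseline variables in the abstinence model also suggests that the two named covariates are regarded as baseline, which Table 1 contradicts.

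**Working it through.** The plan states no figure on this point, so the check is one of timing, of plausible routes from arm to covariate, and of what adjustment does algebraically.

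**1. Timing**

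| Variable | Model | Before randomisation? | First recorded |
|---|---|---|---|
| Baseline depression | PHQ-9, fixed | Yes (Baseline 1 and 2) | Baseline 1 |
| Cardiac rehabilitation attendance | PHQ-9, fixed; abstinence, named | No | 12 weeks |
| Outside depression treatment | PHQ-9, fixed | No | 12 weeks |
| Outside cessation treatment | Abstinence, named | No | 12 weeks |

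People already in depression or cessation counselling are excluded at entry, so counselling of that kind recorded later began after entry. Outside medication is also counted, and some of it may predate randomisation, but Table 1 has no pre-randomisation record that would separate the two.

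**2. Can arm change them?** Three routes are visible in the text.

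- Control session 2 is guided by a booklet covering, among other things, "what happens after a heart attack (i.e. medications, lifestyle changes, cardiac rehabilitation". BAT-CS participants receive the same booklet only to read on their own. This could raise attendance in the control arm.
- BAT-CS sets 2 to 4 activation goals per session through session 5. This could raise attendance in the BAT-CS arm.
- Persistent low mood or continued smoking can lead people to seek outside treatment. An arm that improves these outcomes may therefore change outside treatment as a result.

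The first two routes push in opposite directions. The document gives no uptake data by arm, so the net difference is unknown and could be near zero.

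**3. What adjustment does.** Take a linear model with arm A, covariate M and an unmeasured cause U (motivation, for example) that is independent of A by randomisation:

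- M = m₀ + aA + hU + v
- Y = y₀ + cA + bM + gU + e

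The total effect of arm is c + ab. Let δ be the slope of U on M within arm. Regressing Y on A and M gives M the coefficient b + gδ and gives A the coefficient c − agδ. Therefore

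adjusted − total = (c − agδ) − (c + ab) = −a(b + gδ).

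The term −ab is the part of the treatment effect removed. The term −agδ is bias through the shared cause, and it can appear even when b and c are both zero.

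**4. Reading the result**

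- If a = 0, the difference is zero and the linear estimate is unaffected.
- If a ≠ 0, the sign depends on a and on b + gδ. Suppose attenders have lower PHQ-9, so that b + gδ < 0. If BAT-CS raises attendance (a > 0), adjustment makes BAT-CS look less effective. If control education raises it (a < 0), adjustment makes BAT-CS look more effective.
- For outside treatment, b + gδ may be positive, because people doing badly seek it. The direction then reverses for the same sign of a.

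The document supplies none of a, b, g or δ, so no magnitude is given here. The abstinence model uses a logit link, so this identity does not carry over exactly, but the same two mechanisms apply.

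**The case against.** The strongest defence is that the investigators want the effect of BAT-CS net of co-interventions. That is a legitimate but different question. It requires that no unmeasured cause be shared by the covariate and the outcome, and the protocol neither states that target nor defends that assumption. Pathway questions already have an exploratory place under Mediator analyses.

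A second defence stands in part: nothing in the document shows that arm changes these variables, both arms receive the booklet, and without such a change the linear estimate is essentially the same. But uptake by arm cannot be known before the data are in, and the model should not depend on it.

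A reader might also infer more than the text supports:

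- **That participants without follow-up are lost because of these covariates, so that intent-to-treat is broken.** The covariates are collected at the same visits as the outcomes, so someone with no follow-up lacks the outcome as well. Missing data defines intent-to-treat by who is included and plans inverse probability weighting and pattern mixture models. The adjustment changes what is estimated, not who is analysed.
- **That both models adjust unconditionally.** Only the PHQ-9 model is explicit. In the abstinence model the imbalance and p < 0.10 condition reads as attached to the other baseline variables, which makes inclusion of the two named covariates the likelier reading but not a certain one.
- **That treatment dose, diet, exercise and medication adherence also enter the primary models.** Potential confounders says only that control will be as needed, and Primary outcome analyses names none of them. Diet, exercise and adherence also have Baseline 1 values, which could properly be used.
- **That the effect is known to be diluted by some stated amount.** Without uptake figures, any such number would come from assumed inputs alone.

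**Conclusion.** The point holds as one of timing and estimand. The PHQ-9 model certainly, and the abstinence model on its most natural reading, conditions on variables recorded only after randomisation under a confounding rationale that cannot apply to them. The same specification carries over to the parallel secondary models. If arm alters rehabilitation attendance or outside treatment, the arm coefficient departs from the total randomised effect that Aim I asks about, by an amount and in a direction that this document cannot settle. If arm does not alter them, the PHQ-9 estimate is essentially unchanged. The conclusion rests on Table 1 being the complete measurement schedule for these three items and on the arm-to-covariate routes being plausible, not demonstrated. Adjustment for baseline PHQ-9 is proper and is not in question.

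**What to change.** In Primary outcome analyses, remove cardiac rehabilitation attendance and outside depression treatment from the PHQ-9 model, and rehabilitation attendance and outside cessation treatment from the abstinence GEE. Make the same change in the similar and parallel secondary models. Restrict covariates to pre-randomisation variables, for example baseline PHQ-9 and the stratification factors (PHQ-9 at or above 10, study patch use before randomisation, recruitment site).

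Report rehabilitation attendance and outside treatment by arm at each follow-up. If an estimate adjusted for them is wanted, present it as a labelled sensitivity analysis that plays no part in the efficacy conclusion. In Potential confounders, describe variables first measured after randomisation as co-interventions or process measures.

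The cost is a change of wording, best dated and made before anyone sees outcome data by arm. It needs no new data, visits or participants.

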#### Baseline measures

After consent, participants will complete an initial baseline assessment (i.e., “Baseline 1”; See Table 1) consisting of interview questions and self-report questionnaires. Socio-demographic variables collected by self-report at baseline will be used to describe the sample and include: age, gender, ethnicity, employment, and income. Medical history will be assessed through self-report and chart review and will include: (1) diagnosis, treatment, and length of stay for current admission; (2) detailed history of cardiac disease, events, procedures, and treatments (e.g., revascularization); and (3) co-morbid conditions. Smoking history, including current and past smoking, age of smoking onset, and average number of cigarettes per day will be assessed via a self-report. Use of other tobacco products will be assessed by self-report. Nicotine Dependence will be measured using the Fagerström Test for Nicotine Dependence [50] (FTND). Motivation to quit will be measured using the contemplation ladder [51]. A second, brief baseline assessment will be conducted 1 week following hospital discharge and immediately prior to randomization to condition (i.e., “Baseline 2,” See Table 1). This assessment will include assessments of motivation to quit/stay quit [51] and nicotine withdrawal as baseline variables [52]. Both Baseline 1 and Baseline 2 assessments include assessments of outcome variables (see Table 1 for timing, see outcome measures sections below for a full description of all outcome variables).

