#### Randomization

Randomization will occur 1 week after hospital discharge, immediately after the Baseline 2. We will stratify randomization on elevated symptoms of depression (Patient Health Questionnaire [53] [PHQ-9] score of ≥ 10 vs. < 10 as measured immediately prior to randomization), use of the study provided nicotine patch between discharge and randomization (i.e., using patch vs. not using patch), and recruitment site (i.e., recruited at primary hospital site vs. hospitals subcontracted for recruitment). The randomization sequence will be generated using a stratified permuted block randomization procedure, with small, random sized blocks. The sequence was generated by the study biostatistician. Only the biostatistician and database manager will have access to the randomization sequence and all other study personnel will remain blind to this sequence. Counselors will randomize participants immediately before initiating Session 2 by entering the participant’s identification number, PHQ-9 score, use the nicotine patch, and recruitment site into REDCap [48, 49]. The REDCap interface will indicate the treatment assignment and the counselor will immediately inform the participant of their treatment condition.

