#### Mood and quality of life outcomes

The primary outcome of depressed mood will be assessed using the PHQ-9 [53], a well-established self-report measure of depression in medical populations. A PHQ-9 score ≥ 10 is a well-established cut off indicating likely clinical depression. Secondary mood and quality of life outcomes will include the 10-item Center for Epidemiologic Studies Depression Scale [66] (CESD-10). The CESD-10 is included as a secondary outcome because it has a timeline of only 1 week and thus can give a better measurement of post-discharge, pre-randomization depressed mood (i.e., mood in the time period between Session 1 and randomization)**.** We will measure positive and negative affect using the 10-item Positive Affect Negative Affect Scales [67] (PANAS). Low levels of positive affect represent one aspect of anhedonia (i.e., low levels of positive emotions). We will also measure reactive anhedonia (i.e., blunted response to the occurrence of pleasurable events) using the Snaith Hamilton Pleasure Scale [68, 69] (SHAPS). Stress will be assessed using the Perceived Stress Scale [70] (PSS-4). Health Related Quality of Life will be measured using the 12-Item Short Form Health Survey [71] (SF-12).

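### The PHQ-9 primary model leaves its baseline depression covariate undefined, and its covariate rule excludes prognostic pre-randomisation mood values that happen to be balanced

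*Protocol article*

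**What the plan says.** The Protocol article, Primary outcome analyses, fits mixed models to PHQ-9 at end of treatment and the later follow-ups, "controlling for baseline depression, cardiac rehabilitation attendance, depression treatment outside of the study". It then admits "any other variables not balanced by randomization that are correlated with depressed mood at follow-ups at a modest" threshold of p < 0.10. A further variable must therefore meet two conditions: imbalance between arms, and correlation with the outcome.

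There are two pre-randomisation assessments, and the Baseline measures section states: "Both Baseline 1 and Baseline 2 assessments include assessments of outcome variables". Table 1 confirms this: PHQ-9, CESD-10, PANAS and SHAPS are each marked at Baseline 1 and Baseline 2. Baseline 1 normally takes place in hospital but may be up to a week after discharge. On Baseline 2 the text says: "A second, brief baseline assessment will be conducted 1 week following hospital discharge and immediately prior to randomization to condition".

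The Randomization section stratifies on a PHQ-9 "score of ≥ 10 vs. < 10 as measured immediately prior to randomization", which is the Baseline 2 value. The Mood and quality of life outcomes section justifies CESD-10 partly because its one-week window "can give a better measurement of post-discharge, pre-randomization depressed mood".

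**The concern.** Four measurements (two scales at two visits) fit the term baseline depression, and they are not interchangeable. Discharge, and usually Session 1, fall between the two visits. If Baseline 1 PHQ-9 were used, the named covariates would omit the value closest to randomisation, which also defines the randomisation stratum. If Baseline 2 PHQ-9 were used alone, the earlier PHQ-9 and the CESD-10 would be left aside, although the article gives the CESD-10 a specific pre-randomisation purpose.

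The entry rule adds to this. A prognostic covariate reduces residual variance whether or not it is balanced, so making imbalance a condition of entry discards that benefit. Balance on the other mood values is likely, because randomisation is stratified on a closely related one. The rule also makes covariate choice depend on outcome data. At stake are some precision on a primary outcome and an analyst choice that the article's text does not close.

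**Working it through.** **The plan's own figure.** The Power section states 80% power for f squared = 0.03 with 324 participants. Using a noncentral F test with noncentrality 0.03 × 324 = 9.72 and alpha 0.05, power is 80.0% with 2 numerator degrees of freedom and 87.5% with 1. With 1 degree of freedom, 80% power needs 264 participants, and 264/324 = 81.5% lies inside the stated 80–85% retention. The stated power reproduces, so nothing below corrects it.

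**Inputs for the precision question.** The documents give no correlations. All of these are assumptions:
- Baseline 1 PHQ-9 with follow-up PHQ-9: 0.40–0.50
- Baseline 2 PHQ-9 with follow-up: 0.50–0.55
- Baseline 2 CESD-10 with follow-up: 0.50–0.52
- Baseline 1 with Baseline 2 PHQ-9: 0.60–0.70
- Baseline 1 PHQ-9 with Baseline 2 CESD-10: 0.50–0.60
- Baseline 2 PHQ-9 with Baseline 2 CESD-10: 0.75

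**Formulas.** Residual variance as a share of total is 1 − r′R⁻¹r, where r holds the covariate–outcome correlations and R the correlations among covariates. The ratio is the residual variance with one covariate divided by that with all three. For an effect that has 80% power under the single-covariate model, power with all three is Φ(2.80 × √ratio − 1.96).

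**Worked example.** Take r = (0.45, 0.55, 0.52) for Baseline 1 PHQ-9, Baseline 2 PHQ-9 and Baseline 2 CESD-10, with covariate correlations 0.65, 0.60 and 0.75.
- Baseline 1 PHQ-9 alone: 1 − 0.45² = 0.798
- Baseline 2 PHQ-9 alone: 1 − 0.55² = 0.698
- Both PHQ-9 values: 1 − (0.2025 + 0.3025 − 2 × 0.45 × 0.55 × 0.65)/(1 − 0.65²) = 1 − 0.18325/0.5775 = 0.683
- All three: 0.663
- Ratio against Baseline 1 alone: 0.798/0.663 = 1.20, so 80% becomes about 87%
- Ratio against Baseline 2 PHQ-9 alone: 0.698/0.663 = 1.05, so 80% becomes about 82%

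**Range over the assumed inputs.** Against Baseline 1 PHQ-9 alone the ratio runs from 1.10 to 1.26. Against Baseline 2 PHQ-9 alone it runs from 1.03 to 1.16.

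**Less favourable inputs.** The second range depends on CESD-10 predicting follow-up almost as well as PHQ-9 does. Keep the example's covariate correlations and set r = (0.40, 0.55, 0.45): residual variance is 0.698 against 0.692, a ratio of about 1.01. With r = (0.45, 0.60, 0.50) it is 0.640 against 0.630, a ratio of about 1.02. The lower end for Baseline 2 PHQ-9 is therefore about 1.01.

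| Ratio | Power, from 80% |
|---|---|
| 1.01 | 80.4% |
| 1.05 | 81.9% |
| 1.10 | 83.6% |
| 1.16 | 85.5% |
| 1.20 | 86.6% |
| 1.26 | 88.2% |

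**Sensitivity to a different set-up.** A second calculation used all four PHQ-9 and CESD-10 values, the mean of four follow-ups (assumed intraclass correlation 0.65) and other assumed correlations. Where later values predict better, residual variance falls by 5–8% relative to Baseline 2 PHQ-9 alone and by 20–38% relative to Baseline 1 PHQ-9 alone. In the second comparison, 16–34% comes simply from switching to Baseline 2 PHQ-9. If all four values predict equally well, the fall is 15–28%. The direction is the same, but the size moves with the assumptions.

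**The case against.** The strongest reply is that this is a condensed article and the unseen analysis plan may name the scale and visit. The natural reading is also benign: in a PHQ-9 model, baseline depression most plausibly means Baseline 2 PHQ-9, which is on the outcome's own scale, nearest to randomisation and the basis of the stratum. Adjusting for that value is standard and valid. A second PHQ-9 and a collinear scale are then optional, and under some plausible inputs they add almost nothing. This stands as a limit on size, and the missing definition alone would be little more than a wording query. It does not answer the entry rule, which the article does state: balanced prognostic values are excluded under it as written.

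A reader might also infer that the values left out are more informative than the one used. The documents do not support that. The covariate is undefined, so which values are left out is unknown, and the assumptions above make Baseline 2 PHQ-9 the best single predictor. The remark about CESD-10 concerns measuring mood in the week before randomisation, not predicting PHQ-9 at 3 to 12 months. Nor does the article say outright that only one value enters; that is only the ordinary reading of the phrase.

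**Conclusion.** The point holds as a modest improvement to the analysis of a primary outcome. The covariate is not identified, and the stated rule leaves out balanced but prognostic mood values that are already collected. Compared with a model using all three values, residual variance is about 1–16% larger with Baseline 2 PHQ-9 alone and about 10–26% larger with Baseline 1 PHQ-9 alone. An effect with 80% power under the single-covariate model would have about 80–85% or 84–88% respectively. These sizes rest wholly on assumed correlations.

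The larger stake is ruling out Baseline 1 alone and settling the choice in advance. It would be wrong to conclude that the trial is underpowered for PHQ-9, since the stated 80% reproduces. It would also be wrong to conclude that the choice is known to remain open after the data are seen, since a plan not shown may close it.

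**What to change.** Before unblinding, replace the unspecified term with named covariates: continuous Baseline 2 PHQ-9 as the core covariate, plus Baseline 1 PHQ-9 and Baseline 2 CESD-10, all fixed and entered regardless of balance or observed correlation. In the parallel CESD-10, PANAS and SHAPS models, enter both pre-randomisation values of the outcome concerned. No gain has been calculated for those secondary models; the reasoning simply carries over. If the analysis plan already names a covariate, check it against this list and align the article's wording.

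All these values precede randomisation, so adjusting for them introduces no post-treatment bias. The cost is a change of wording, two extra parameters in the PHQ-9 model and a simple stated method for the few missing baseline values. No new data are needed.

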### Aim I

Test the efficacy of BAT-CS versus control on depressed mood and smoking cessation. *Hypothesis 1a*: Patients treated with BAT-CS will demonstrate significantly greater improvements in mood and significantly higher rates of biochemically verified 7-day point prevalence abstinence over 12 months than control patients. This trial is powered for hypothesis 1a analyses. *Hypothesis 1b*: Patients treated with BAT-CS will also have higher rates of 30-day point prevalence and continuous abstinence since discharge and longer time to smoking lapse and relapse than control patients.

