#### Power

The proposed study is fully powered for both Aim I primary outcomes (i.e., biochemically confirmed 7-day point prevalence abstinence and depression symptoms on the PHQ-9 over 12 months post discharge). Based on existing data at the time of study design [36, 38, 86], we expect 7-day point prevalence rates to differ by 8% (29% in control, 37% in BAT-CS) at 12 months, representing an odds ratio of 1.4 at 12 months. We will analyze our data longitudinally (see below), thus we base our sample size on the longitudinal effect across the 4 follow-ups (i.e., end-of-treatment and, 6, 9, and 12 months post discharge). We expect a *longitudinal* odds ratio of 1.33 ending with an 8% between-group difference at 12 months as described above. It is important to note that experts have proposed that increasing rates of smoking cessation in ACS patients by even 5% would have a large impact on public health [87]. Given the assumptions above and an alpha level of 0.05, a total sample size of 324 participants would be required in order to have sufficient (80%) power to test the *longitudinal* effect on intent-to-treat 7-day point prevalence abstinence over 1 year post-discharge. This sample will be more than sufficient (power > 80%) to detect even small longitudinal effects on depression symptoms over 1 year (i.e., with 324 participants we have 80% power to detect between group effect of f squared = 0.03).

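### The only dependence term named for the PHQ-9 model is a subject-specific intercept, without robust errors, so standard errors at single visits can be wrong in either direction; the effect averaged over 12 months is essentially safe

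*Protocol article*

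**What the plan says.** Under Primary outcome analyses, the protocol article plans a series of mixed models "to estimate the effect of BAT-CS versus control on depressed mood (PHQ-9) at end-of-treatment and subsequent follow-ups", adjusted for baseline depression and other covariates. Dependence between a participant's repeated scores is dealt with in one sentence: "Models will include a subject-specific intercept to adjust for repeated measurements within participant over time". On estimation it adds: "Modeling is done using a likelihood-based approach and thus makes use of all available data". It names no random slope, residual structure, visit-specific variance or type of standard error for PHQ-9, and states no group-by-visit term.

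The preceding paragraph handles the other primary outcome differently. Abstinence is analysed by "generalized estimating equations (GEE) with robust standard errors", with "a working unstructured correlation to accommodate within-subject correlation".

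The target is stated elsewhere. Hypothesis 1a, under Aim I, reads: "Patients treated with BAT-CS will demonstrate significantly greater improvements in mood and significantly higher rates of biochemically verified 7-day point prevalence abstinence over 12 months". The Power section bases the sample size on "the longitudinal effect across the 4 follow-ups (i.e., end-of-treatment and, 6, 9, and 12 months post discharge". Secondary outcome analyses applies parallel mixed models to CESD-10, PANAS, SHAPS, PSS, SF-12 and DASI.

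**The concern.** A random intercept with independent, constant-variance residuals implies compound symmetry: the same variance at each follow-up and the same correlation between every pair of follow-ups, whether three or nine months apart. If group effects are estimated separately by visit, the model then gives each of them the same residual variance, namely the average over visits. Where the true variance at a visit is above that average, the standard error there is too small; where it is below, too large.

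The article itself gives some reason to doubt compound symmetry. The exclusion-criteria text explains that patients without baseline symptoms are enrolled because many develop depression after the event, which suggests diverging individual courses. The exploratory analysis of mood and smoking over the same 12 months uses an autoregressive model, which ordinarily implies correlation that weakens with lag.

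At stake are mood effects quoted at 12 weeks or 12 months, statements that the effect grows or fades, and the same statements for the six secondary scales.

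**Working it through.** **The plan's own PHQ-9 figure.** The Power section gives 80% power for f² = 0.03 with 324 participants at alpha 0.05. With noncentrality 0.03 × 324 = 9.72, the noncentral F gives 79.98% with 2 numerator df and 87.5% with 1. The stated figure therefore reproduces with 2 df. It concerns the longitudinal effect and is not disputed here.

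**Inputs.** From the article: four follow-ups (12 weeks; 6, 9 and 12 months), N = 324, alpha 0.05 (taken as two-sided), baseline PHQ-9 as covariate, expected follow-up of at least 80-85%. Assumed, because the article gives none: SDs (relative to 1 at baseline), correlations and a group-by-visit term. Gaps from baseline are 12/52, 26/52, 39/52 and 52/52 of a year.

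**Formulas (complete data).**
- Common baseline slope b = mean over visits of r_t·s_t, where r_t is the correlation with baseline and s_t the SD at visit t.
- Residual variance v_t = s_t² − 2b·r_t·s_t + b².
- Model SE / true SE at visit t = √(mean(v) / v_t).
- Type I error = 2 × [1 − Φ(1.96 × ratio)].

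**Worked case: correlation 0.45^gap, constant SD.** The r_t are 0.832, 0.671, 0.549 and 0.450, so b = 0.625. At 12 weeks v = 1 − 2(0.625)(0.832) + 0.391 = 0.351; at 12 months v = 1 − 2(0.625)(0.450) + 0.391 = 0.828. The four values 0.351, 0.552, 0.704 and 0.828 average 0.609. The ratios are √(0.609/0.351) = 1.32 at 12 weeks and √(0.609/0.828) = 0.86 at 12 months.

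| Assumed structure | SE ratio, 12 wk | Type I, 12 wk | SE ratio, 12 mo | Type I, 12 mo | SE ratio, 12 mo minus 12 wk |
|---|---|---|---|---|---|
| Equal correlation 0.6, constant SD | 1.00 | 5.0% | 1.00 | 5.0% | 1.00 |
| Decay to 0.45 at 12 months, constant SD | 1.32 | 1.0% | 0.86 | 9.3% | 0.78 |
| Milder decay*, constant SD | 1.12 | 2.8% | 0.93 | 6.9% | 0.88 |
| Equal correlation 0.6, SD falling 20% | 0.90 | 7.7% | 1.13 | 2.7% | 0.99 |
| Milder decay*, SD falling 20% | 0.995 | 5.1% | 1.03 | 4.4% | 0.87 |

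*0.8 × (0.3 + 0.7 × 0.3^gap) off the diagonal, that is, a stable component plus a decaying one, with 20% measurement noise. SD falling 20% means 1, 0.93, 0.87 and 0.80 at the four visits.

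Over a wider set of structures, including an SD rising 10%, the ratio runs from 0.90 to 1.41 at 12 weeks and from 0.83 to 1.13 at 12 months.

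**Effect averaged over the four visits.** With complete data the model's variance for a participant's mean is c + (mean(v) − c)/4, where c is the average residual covariance. That equals the true variance of the mean whatever the pattern, so the ratio is 1.000 in every scenario.

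**With dropout.** In 1,500 simulated trials per scenario (N = 324, REML random-intercept fit, monotone missingness rising from 10% to 20%), the averaged effect had SE ratios of 0.97-1.02 and type I error of 4.5-5.9%. The visit-specific pattern stayed close to the table: for decay to 0.45 with constant SD, 1.37 at 12 weeks and 0.83 at 12 months. In a separate simulation with dropout depending on the previous score (1,000 trials per scenario, decaying correlations, 84% retained at 12 months), rejection under no effect was 7-9% at 12 months, 1-2% at 12 weeks, 4-5% for the time average and 6-8% for the group-by-visit test.

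**The case against.** The strongest reply has three parts.

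First, the primary inference is the effect over 12 months, in both Hypothesis 1a and the Power section, and that test holds its level. This stands. A reader might infer that the primary mood test is invalid, or that a 12-month PHQ-9 claim central to the trial would be declared significant too often. The article supports neither: it states no separate 12-month PHQ-9 hypothesis, and the 8-point difference at 12 months in the Power section is for abstinence.

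Second, the article says the models will include an intercept, not that they contain nothing else. It does not say that errors are model-based, it states no group-by-visit term, and an article may leave such detail to the analysis plan. This stands in part. The wording that points to each follow-up can also be read as listing the visits that enter the model. But the sentence gives the intercept the task of handling the repeated measures, and the neighbouring paragraph specifies correlation and error type for abstinence. The article thus states a structure for PHQ-9, and on its natural reading a restrictive one.

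Third, the direction of error depends on inputs the article does not give. This stands fully. It is tempting to say that the 12-month error is always too small and the 12-week error too large, but a shrinking spread reverses or cancels that.

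A reader might also infer bias under dropout, since likelihood methods then rely on a correct covariance. The principle is sound, but no bias has been shown here, and the Missing data section already plans weighting and pattern-mixture sensitivity analyses.

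**Conclusion.** The concern holds for effects at single visits and for change between visits, not for the averaged effect.

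- Decaying correlation with constant SD: the 12-month standard error is about 7-14% too small (type I error about 7-9%) and the 12-week one about 12-32% too large (about 1-3%). The standard error of the difference between those two visits is about 12-22% too small (ratios 0.88 and 0.78).
- SD falling 20% with equal correlation: the direction reverses, with type I error 7.7% at 12 weeks and 2.7% at 12 months.
- Milder decay with SD falling 20%: single-visit errors almost cancel, though the between-visit contrast does not (ratio 0.87).
- Compound symmetry: no error.

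These sizes rest on assumed SDs and correlations, on independent residuals with model-based errors, and on visit-specific effects being taken from this fit. This is a cheap improvement to secondary inference about timing, not a flaw in the primary averaged test.

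**What to change.** Preferred: replace the random intercept with an unstructured residual covariance over the four follow-ups, with visit as a factor, group-by-visit terms and baseline PHQ-9. Name the contrast averaged over the four visits as primary and the visit-specific contrasts as supportive.

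Alternative: keep the random intercept and use robust (sandwich) standard errors, as already planned for abstinence. This repairs the standard errors but leaves the working covariance as it is, so the first option is better where dropout depends on earlier scores.

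Apply the same choice to the parallel secondary-outcome models.

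The cost is one line of specification. A 4 × 4 unstructured covariance has 4 × 5 / 2 = 10 parameters against 2 for the random-intercept model, which 324 participants support easily, and little is lost if compound symmetry holds.
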